### Objectives

The main objectives of this study are: (1) to design and implement a *serious game* called *emoTICare* to promote physical and emotional health, as well as the development of socio-emotional skills among adolescents with Type 1 Diabetes Mellitus (T1DM) through a psychological intervention conducted on a technological platform that incorporates artificial intelligence and Ecological Momentary Assessment (EMA); (2) to analyze the effectiveness of this *serious game* on indicators of disease adjustment, quality of life, and socio-emotional well-being, as well as improvements in socioemotional competencies and skills.

The study hypothesizes that adolescents will maintain or improve their physical and emotional health indicators following the *emoTICare* program. Specifically, statistically significant improvements (*p* ≤ .05) are expected in the following variables: health-related quality of life, social skills and communication, emotional awareness, resilience, self-esteem, as well as coping and problem-solving abilities. Additionally, a statistically significant reduction (*p* ≤ .05) is anticipated in variables related to the perceived threat of the disease, as well as emotional and behavioral problems. The experimental group is expected to show improvements in all these areas when comparing pre- and post-treatment evaluations, and also in comparison to the control group on the waiting list.

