## Materials and methods

### Study design

A clinical longitudinal experimental design with inter-subject comparisons was employed, with the aim of comparing an experimental group (i.e., individuals receiving psychological treatment) and a control group on the waiting list (i.e., those without treatment) at three time points: before treatment (T1), and two post-treatment time points (T2, T3). The control group hasn’t any alternative activities or exposure to placebo-like interactions. Furthermore, an intra-subject analysis was conducted by comparing repeated measures to observe changes within the same individuals before (with pre-treatment measurements, T1), after 6 weeks (T2, in the control group and post-treatment in the experimental group), 6 months after T2 (T3, in the control group and post-treatment in the experimental group).

Initially, immediately after completing the informed consent online, a first evaluation will be conducted for all participants (T1), covering the main areas that constitute the psycho-emotional state of the participants. Following this first evaluation, participants in the experimental group will engage in six weeks of gameplay, with each week dedicated to completing one mission of *emoTICare*. At the six-week mark after the initial evaluation, and immediately following the completion of the *emoTICare* application by participants in the experimental group, a second evaluation (T2) of all participating adolescents (control and experimental groups) will take place. Following a period of six months from T2, a subsequent measurement, designated T3, will be conducted in all participants.

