The principal investigator will be responsible for obtaining informed consent from the participants (adolescents and parents/legal guardians) by informing them about the study. Adolescents aged between 12 and 16 inclusive will be required to sign the consent form in conjunction with their guardian, while those aged 16 and over will be permitted to sign it directly.

The collection of data will be facilitated through the utilisation of the Limesurvey platform, wherein the participants will be prompted to complete questionnaires in an anonymous manner. The principal investigator will supervise access and data security, and the research team will only access anonymised data for analysis.

The research team will measure baseline data at the commencement of the study through online questionnaires, and also the two post-test measures. The randomisation process will be overseen by the principal investigator and team, and will be conducted using a computerised random number generator.

The research team will be responsible for configuring and training participants and staff on the use of the Limesurvey platform, ensuring proper usage of the system.

According to the Standard Protocol: Recommendations for Interventional Trials statement [49], the current study protocol outlines the details of the study rationale, objectives, interventions, methods and statistical analyses, organization, and ethical considerations (See Figs 1 and 2).

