The phase encompassing the evaluation of the variables of interest, T1-T2-T3, will take place through the survey platform of the Universitat de València, Limesurvey, from September 2024 to the end of February of 2027. The response platform for the questionnaire battery includes a consent form for anonymous participation in the study. In this platform, informed consent will be obtained from the parents or legal guardians of the participants, as well as from the minors themselves, ensuring that all are informed about the anonymity and confidentiality of their data, confirming that their participation in the study is voluntary.

To access and play the *emoTICare serious game* online for six weeks (one week per mission of the game), participants will be provided with a link at the end of the evaluation survey conducted at T1. This *serious game* contains six distinct areas, each designed to be completed within a maximum of one week, thus allowing sufficient time to progress at different paces. During the period in which the adolescents are completing the *serious game*, an email address and a mobile phone number will be made available for participants to contact in case they need assistance (see Table 1).

**Table 1 pone.0325763.t001:** Intervention timeline.

				Timeline (in months)																															
	2024							2025												2026												2027			
	Jun	Jul	Aug	Sep	Oct	Nov	Dec	Jan	Feb	Mar	Apr	May	Jun	Jul	Aug	Sep	Oct	Nov	Dec	Jan	Feb	Mar	Apr	May	Jun	Jul	Aug	Sep	Oct	Nov	Dec	Jan	Feb	Mar	Apr

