### Assessment tools

#### Clinical and sociodemographic variables.

Sociodemographic variables such as gender, age, nationality, previous contact with psychology professionals, and reason for consultation will be assessed using an ad-hoc record after informed consent has been obtained.

Additionally, to gather relevant data related to the illness and its impact on adolescents, an ad-hoc record will collect the following medical variables:

Glycated Hemoglobin (HbA1c)Cause and number of hospitalizations due to diabetesMonths since the onset of the diseasePerceived difficulty due to the illnessSpecific aspects of diabetes causing the most difficultyPresence of other medical conditionsPresence of psychological disordersType of medical treatment received for T1DMPhysical consequences of T1DM

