### Measurements

Missing data will not be an issue, as the survey is conducted through LimeSurvey, where all questions are mandatory and cannot be skipped by participants.

To be included in the data analysis, participants must have completed all three measurement points and answered all questionnaires.

T1: First measurement: After the participant had signed the informed consent, the initial score for this outcome was assessed.T2: Second measurement: POST Up to 6 weeks after the second measurement, the second measurement of the same variable was carried out.T3: Third measurement: POST Up to 6 months after the second measurement, the third measurement of the same variable was carried out.

[Time Frame: Baseline up to 30 weeks]

Primary Outcome Measure:

Change Quality of Life (measured by KIDSCREEN-27).Change Emotional and Behavioral Problems (measured by SDQ).Change Emotional Competences (measured by EAQ-30).Change Self-concept (measured by CAG)Change Coping (measured by SPSI-R).Change Social Skills (measured by CHASO).

Secondary Outcome Measure:

Change Threat of disease (measured by BIP-Q)Change Psychoeducation Diabetes

Psychoeducation of the disease: the ECODI Diabetes knowledge scale will be used to assess this variable [79]. This scale consists of 25 items and four dimensions: basic knowledge and self-care, laboratory values, diet and physical exercise. It is a scale that is corrected by the number of hits and misses.

[Time Frame: Start of the game and during the game]

Change Resilience (measured by CD-RISC).

Other Pre-specified Outcome Measures:

Glycaemic control

HbA1c: It will be used to evaluate the glycemic control of the diabetic patient in endocrinology diseases.

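### HbA1c appears to be a mandatory survey item with no test date recorded, so a six-week T2 value may be an old result re-entered and cannot be tied to the intervention period

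*Protocol article*

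**What the plan says.** Under Other Pre-specified Outcome Measures in the Measurements section, glycaemic control has a single entry: "HbA1c: It will be used to evaluate the glycemic control of the diabetic patient in endocrinology diseases". No time frame is attached to it.

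The section on clinical and sociodemographic variables says that "an ad-hoc record will collect the following medical variables". HbA1c heads that list, and the date of the test is not on it.

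On data capture, the Study design section says: "The collection of data will be facilitated through the utilisation of the Limesurvey platform". It describes baseline and both later measures as online questionnaires, and no trial blood test is mentioned. The Measurements section adds that "all questions are mandatory and cannot be skipped by participants", and concludes from this that missing data will not arise. It also limits the analysis to participants who completed all three time points and every questionnaire.

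On timing, T2 takes place "At the six-week mark after the initial evaluation". The game starts no earlier than T1, because "participants will be provided with a link at the end of the evaluation survey conducted at T1". T3 follows six months after T2. Both arms are assessed at the same times.

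The Objectives state that "adolescents will maintain or improve their physical and emotional health indicators following the" programme. No margin defines what counts as maintained.

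**The concern.** A psychological questionnaire can be answered afresh on any day. HbA1c changes only when blood is drawn, and the plan relies on whatever test the participant last had. Where no test has been done since T1, a mandatory field leaves two options: type the old value again or guess. A repeated value gives a change of exactly zero. With no date recorded, the analyst cannot tell it from a new test with the same result. The mandatory rule therefore hides missing HbA1c data instead of preventing it.

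HbA1c also looks backwards. A test done on the T2 date still averages in some of the period before the game began.

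Both effects operate in both arms, so they shrink any T2 difference toward zero. The design also plans comparisons within subjects over time. There, a flat HbA1c could be taken as support for the maintained part of the hypothesis when the measurement had little chance to move in either direction.

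**Working it through.** The plan gives no figure for HbA1c (no effect size, margin, averaging window or testing interval), so there is nothing to reproduce. The check asks how much of a reported value describes the time before the game.

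**Inputs from the protocol article**
- Time from game start to T2: e = 6 weeks at most.
- Time from game start to T3: e = 6 + 26 = 32 weeks. The time frame in Measurements says up to 30.

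**Assumptions, not in the documents**
- HbA1c averages glycaemia over W = 8 to 12 weeks.
- The test is a weeks old when entered.
- Where an average over participants is taken, a is uniform over a testing interval of V = 13 or 26 weeks.

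**Formulas.** Let x = min(max(e − a, 0), W).
- Flat weights: pre-game share = 1 − x/W.
- Recency weights (declining linearly into the past): pre-game share = (1 − x/W)².

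**T2 (e = 6)**

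| Age of test | Flat, W = 8 | Flat, W = 12 | Recency, W = 8 | Recency, W = 12 |
|---|---|---|---|---|
| Same day | 1 − 6/8 = 25% | 1 − 6/12 = 50% | (2/8)² = 6% | (6/12)² = 25% |
| 4 weeks | 1 − 2/8 = 75% | 1 − 2/12 = 83% | (6/8)² = 56% | (10/12)² = 69% |
| 6 weeks or more | 100% | 100% | 100% | 100% |

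**T2, averaged over routine testing**
- Tests that predate T1: (13 − 6)/13 = 54% for V = 13, and (26 − 6)/26 = 77% for V = 26.
- Mean pre-game share with flat weights is 1 − 18/(W·V). For V = 13 this is 83% (W = 8) to 88% (W = 12); for V = 26 it is 91% to 94%.
- With recency weights it is 74% to 81% for V = 13, and 87% to 90% for V = 26.
- So if a true effect were present in full from T1, the T2 contrast would show at most about 100 − 74 = 26% of it under these testing intervals, and as little as 6%.

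**T3 (e = 32)**
- Any test up to 13 weeks old: pre-game share 0%.
- Contamination starts only when a exceeds 32 − W, that is 24 weeks (W = 8) or 20 weeks (W = 12). If T3 falls at week 30, the limits are 22 and 18 weeks.
- With V = 26 and flat weights, the mean share is 1% (W = 8) to 6% (W = 12).

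**Choosing a cut-off for T3.** Requiring only that the test is dated after T2 would admit a week-7 test, whose pre-game share is 1 − 7/12 = 42% (flat, W = 12). Requiring at least 12 weeks after T1 brings the share to 0% for every W up to 12.

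**The case against.** The strongest reply is that much of this is inference from a condensed article. The text does not say that the ad-hoc record sits inside LimeSurvey, or that it is repeated at T2. The primary and secondary outcomes are labelled as changes, and HbA1c is not. Test dates and recency limits are form-level details that a full protocol may contain. This stands in part. Repetition within the survey is a reasonable inference, because all three measurements are described as online questionnaires and an outcome has to be measured after baseline, but it is not stated. The point does not rest on omission alone, however: the mandatory-answer rule and the list of recorded variables are printed, and together they would produce undetectable stale values.

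Second, a reader might infer that HbA1c will show maintained control by construction. The documents do not support that. It holds only for a value that is re-entered or predates the game. A fresh T2 value is diluted, not fixed, and at T3 the dilution largely disappears.

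Third, a reader might infer that the physical-health hypothesis stands or falls with HbA1c. It is not among the variables named for significance at p ≤ .05, the covariance analyses concern Likert composites, and no success rule for HbA1c is stated. KIDSCREEN-27 Physical Well-Being and hospitalisations are also collected. That an unchanged value would be read as success is a risk, not something the plan says.

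Finally, the percentages depend on an averaging window and testing schedule from outside the documents. That is correct, and it is why they are given as ranges under two weightings.

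**Conclusion.** The concern holds in a limited form. As described, an HbA1c value reported at T2 cannot be tied to the intervention period, and the mandatory rule would make old or guessed values look like complete data.

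On assumed 8–12 week averaging, a same-day T2 test is 25–50% pre-game with flat weights, or 6–25% with recency weights. A test six or more weeks old is wholly pre-game under any window. The averages over participants also need an assumed testing interval and carry less weight. The consequence is a T2 contrast between arms pulled toward zero, and a within-arm change that could be mistaken for stable control. T3 is sound provided that the test is reasonably recent.

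The conclusion assumes that HbA1c is self-reported in the survey and asked again at T2. Severity is minor: HbA1c is listed after the primary and secondary outcomes, and none of them depends on it.

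**What to change.** - Record the test date with every HbA1c value.
- Exempt this item from the mandatory rule by offering an answer such as no test since the last questionnaire. State that this answer does not make a participant incomplete for the other outcomes, and that it is not filled by the last-observation-carried-forward method in the Data analysis section, which would restore the same artificial zero change.
- Set a maximum age for the T1 value.
- Make T3 the main HbA1c time point, compared between arms and adjusted for T1. Count only tests dated late enough for the averaging window to lie after the game began, for example at least 12 weeks after T1, and state that this is an assumption.
- Report dated T2 values descriptively only, and report the number with an eligible value by arm.
- State that an unchanged HbA1c is not by itself evidence of maintained control.

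The cost is one date field, one response option and a short outcome definition, with no extra blood test. The HbA1c sample will be smaller. Those with an eligible test may also be a selected group, possibly differently in each arm, which is why the counts by arm are needed. According to the timeline, T3 assessment runs to February 2027, so later entries can still be dated. Undated entries from anonymous respondents may not be recoverable.

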### Data analysis

In the present study, the per-protocol analysis (PP) approach was utilized to evaluate the effectiveness of the treatment and the management of missing data. This method includes only participants who fully adhered to the study protocol, ensuring that the results reflect the true efficacy of the intervention under ideal conditions. Participants will be included in the main analyses only if they have completed the treatment as per the protocol, that is to say, if they have adhered to all instructions without significant interruption. Participants who withdraw or fail to complete the treatment will be excluded from the analyses. This methodological decision is underpinned by the principle of minimizing potential bias from missing data, thereby ensuring that the results of the study accurately reflect the outcomes of participants who adhered to the treatment protocol. To address the issue of missing data during follow-up or treatment, predefined procedures will be implemented. The last observation carried forward (LOCF) imputation method will be employed to address missing data, with the last available measurement being utilised to complete the missing values. Furthermore, sensitivity analyses will be conducted to assess the impact of missing data on the study outcomes. These procedures are designed to minimise data loss, maintain the internal validity of the study, and ensure the robustness of the results.

Several statistical analyses will be performed to determine the effectiveness of *emoTICare*. As a first step, chi-square tests and t-tests were performed to examine potential differences between the control and experimental groups in key demographic and clinical variables (e.g., age, gender, disease duration). Although randomization is expected to ensure comparability, these tests were conducted to verify baseline equivalence. Propensity Score Matching (PSM) was not used to adjust for baseline differences, as the study followed a randomized controlled design.

Additionally, chi-square tests will compare the number of participants who withdraw from the experimental group with those who withdraw from the control group, ensuring no significant differences exist.

The primary focus of this study is on the evaluation of the programme’s overall effectiveness, as opposed to the presentation of definitive assertions concerning the outcomes of individual participants. It is imperative to emphasise that the tests are embedded in pre-specified models, with the primary focus being on assessing the overall effectiveness of the programme.

Before testing the change models, descriptive analyses, Pearson correlations, and multivariate and univariate analysis of variance (MANOVA and ANOVA) will be conducted using pre-intervention scores for participants in experimental and control groups to identify potential baseline differences. Furthermore, multivariate and univariate analysis of covariance (MANCOVA and ANCOVA) will be performed to detect changes in post-intervention scores (short-term effect), with pre-intervention scores as a covariate. These analyses will focus on latent variables derived from the composite scores of multiple Likert items, which represent underlying constructs such as emotional symptoms or health-related quality of life. Effect sizes (Cohen’s *d*) for each variable will also be calculated to estimate the magnitude of differences between the experimental and control groups. These analyses will be conducted using SPSS V.28.

To ensure the reliability of the results, we will begin with a series of diagnostic tests and validation procedures. This will include an analysis of residuals to assess the goodness of fit of the model, using residual plots and tests for normality (e.g., Q-Q plots and Shapiro-Wilk test). Homoscedasticity will be evaluated through the Breusch-Pagan or White’s test, and the Durbin-Watson statistic will be used to check for autocorrelation in the residuals. These tests will allow us to ensure that the assumptions of the parametric models are met. Additionally, we will conduct cross-validation (k-fold) to ensure that the model generalizes well to unseen data and is not overfitted. We will also perform outlier detection using Cook’s distance and leverage plots to examine the influence of individual data points on the model.

Multiple hierarchical regression analyses will be conducted to examine the added predictive value of the experimental condition in explaining the intervention program’s efficacy. Hierarchical regression is a stepwise method where predictors are added to the model in blocks. The rationale behind the hierarchical approach is to assess the incremental contribution of each new block of predictors while controlling for the variables entered in the previous blocks. This allows for a clearer understanding of the unique variance explained by the experimental condition, after accounting for initial factors.

Step 1: The first block typically includes variables measured at time 1 that are believed to influence the dependent variable (i.e., the change between T2-T1 and T3-T1 for each variable). These could include baseline measures of emotional symptoms, quality of life, or disease-related factors.

Step 2: In subsequent blocks, new independent variables (predictors) are added. For example, in the second block, we would add the experimental condition (treatment vs. control) to assess its impact on the change in the dependent variable, controlling for the baseline scores. The dependent variable will be the change between pre- and post-intervention scores, as well as between pre-intervention and follow-up scores. A statistically significant change in the coefficient of determination in Model 2 (predictor: experimental condition, controlling for pre-intervention score) will be interpreted as added predictive value. A significant prediction from the experimental condition, controlling for pre-intervention score, will allow attribution of significant change to the intervention.

The Reliable Change Index (RCI) will be calculated for the scores of the evaluated variables. Reliable change will be determined by the extent to which an individual’s progress exceeds the natural fluctuation of measurements [80]. The RCI will be calculated using pre- and post-*emoTICare* means, along with the pre-intervention standard deviation and Cronbach’s alpha index.

Following completion of the *emoTICare* program, statistically significant improvements (*p* ≤ .05) are expected in scores related to health-related quality of life, social and communication skills, emotional awareness, resilience, self-esteem, as well as coping and problem-solving skills. Conversely, a statistically significant reduction (*p* ≤ .05) is anticipated in variables associated with perceived disease threat, as well as emotional and behavioral problems.

An independent data safety monitoring board (DSMB) is to be convened at six-month intervals in order to review serious adverse event (SAE) reports. Should the DSMB determine that there is no association between the serious adverse events and the intervention under evaluation, the study may proceed. Conversely, if the events are found to be associated with the intervention, the DSMB is able to implement measures to ensure the safety of participants. In the event of the identification of serious adverse events, the DSMB may take the following actions: to halt the study, modify the protocol, adjust the treatment, enhance monitoring, or recommend early termination, with the overarching aim of ensuring participant safety.

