Adolescent **self-concept** will be assessed using the latest version of the ***Garley Self-Concept Questionnaire*** (CAG) by García Torres [77]. This instrument aims to measure self-concept from a multidimensional perspective in adolescents. It consists of 48 Likert-type items, providing a global self-concept score, and is divided into six subdimensions: *Physical Self-Concept*, *Social Acceptance, Family Self-Concept*, *Intellectual Self-Concept*, *Self-Evaluation*, and *Sense of Control*. The questionnaire shows adequate psychometric properties for both the global score (α = 0.87) and the subscales.

Lastly, as a control variable, the ***Oviedo Infrequency Response Scale*** will be administered, developed by Fonseca-Pedrero et al. [78]. This scale consists of 12 Likert-type items (1–5) that are distributed throughout the questionnaire at key points. The items are organized into three groups of four, coded according to the questionnaire variable in which they are integrated. If a subject answers three or more items incorrectly, their questionnaire responses will be invalidated.

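### The only named main analysis keeps per-protocol, three-wave completers, and its treatment-completion rule can remove only game-arm adolescents, so randomisation does not protect the arm comparison

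*Protocol article*

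**What the plan says.** The Data analysis section sets the main analysis population by adherence: "Participants will be included in the main analyses only if they have completed the treatment as per the protocol". It then adds: "Participants who withdraw or fail to complete the treatment will be excluded from the analyses". The Measurements section adds a second filter: "To be included in the data analysis, participants must have completed all three measurement points and answered all questionnaires".

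Under Study design, the experimental arm plays for six weeks, one mission a week. The waiting-list arm is described as not having "any alternative activities or exposure to placebo-like interactions".

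The Data analysis section justifies the exclusion as a way to reduce bias from missing data. It also announces LOCF imputation and unspecified sensitivity analyses on missing data. As a check on attrition it offers a test of counts: "Additionally, chi-square tests will compare the number of participants who withdraw from the experimental group with those who withdraw from the control group". A significant coefficient for experimental condition, adjusted for the pre-intervention score, "will allow attribution of significant change to the intervention". The same section describes the focus as the programme's overall effectiveness. The Discussion concedes only that per-protocol analysis ignores real-world problems of adherence.

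**The concern.** Randomisation makes the arms comparable as allocated. A filter applied afterwards keeps that comparability only if it acts alike in both arms or is unrelated to outcome. Here a game-arm adolescent must finish six missions and answer three surveys, while a control need only answer the surveys. If those who finish the game are the ones who would have improved anyway, the game arm looks better without any effect of the game. Adjusting for T1 scores removes only the part of this selection that T1 scores explain.

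Every between-arm conclusion is affected, because this is the only main analysis set named and the plan reads the arm coefficient causally. The three-wave rule also discards a valid T2 score from anyone who misses T3, so even the short-term comparison depends on behaviour six months later.

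**Working it through.** **Inputs from the protocol article.** The total is 372 (Sample size), allocated by simple randomisation with equal probability (Study design), so 372/2 = 186 per arm are expected. Anticipated dropout is 20% overall (Sample size), and 186 × 0.8 ≈ 149 per arm would remain.

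**Assumptions not in the document.** These are the completion rate in each arm, a T1-T2 correlation of 0.6, and r, the correlation between the tendency to complete and the baseline-adjusted outcome. The true effect is set to zero.

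**Formulas.**
- The ANCOVA residual SD is √(1 − 0.6²) = 0.8.
- If a fraction d is lost, the mean tendency to complete among those kept is λ(d) = φ(Φ⁻¹(d))/(1 − d). This gives λ(0.1) = 0.195, λ(0.2) = 0.350 and λ(0.3) = 0.497.
- Spurious difference = 0.8 × [r(game) × λ(game) − r(control) × λ(control)].
- The type I error is the two-sided rejection probability at 1.96, given that difference and its standard error of about 0.09 SD.

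**Results.**

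| Completion, game / control | Selection | Spurious difference | Type I error |
|---|---|---|---|
| 70% / 90% | r = 0.3, game arm only | 0.8 × 0.3 × 0.497 = 0.12 SD | about 25% |
| 70% / 90% | r = 0.2, game arm only | 0.8 × 0.2 × 0.497 = 0.08 SD | about 14% |
| 70% / 90% | r = 0.3, both arms | 0.8 × 0.3 × (0.497 − 0.195) = 0.07 SD | about 12% |
| 80% / 80% | r = 0.3, game arm only | 0.8 × 0.3 × 0.350 = 0.08 SD | about 15% |
| 80% / 80% | r = 0.3, both arms | 0 | 5% |
| any | r = 0 | 0 | 5% |
| 70% / 90% | r = −0.3, game arm only | −0.12 SD | about 25%, against the game |

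**Is the exclusion needed for power?** No. For an assumed standardised difference of 0.5, power is 0.998 with 186 per arm and 0.991 with 149.

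**Do the stated safeguards help?**
- *LOCF.* It fills in later scores for people who stopped responding. The two inclusion rules have already removed those people, so the rules cannot all apply.
- *Sensitivity analyses.* They concern missing data, and no all-randomised population is named for them.
- *Chi-square test.* It compares how many withdraw, not why. The fourth row of the table shows this: loss is equal at 20% per arm, so there is nothing for the test to find, yet the error rate is about 15%.

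**The case against.** The strongest objection is to direction and size. Nothing in the protocol article links finishing the game to improving. The Discussion's remarks on fatigue and lost motivation are not confined to players, and the three-wave rule removes controls too. If selection is the same in both arms, the bias shrinks or vanishes. This stands. A reader might infer that the analysis must favour emoTICare, or that the error rate must exceed 5%, but the document supports only that both are likely.

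A reader might also infer that the chi-square test is worthless. That goes too far. With 10% versus 30% loss and 186 per arm, its power is above 99% if non-completers are counted as withdrawals, so a gross imbalance would be seen. Detecting an imbalance does not correct it, however, and a non-significant result does not show that the remaining groups are comparable.

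It can also be said that the plan openly states an ideal-conditions efficacy aim, lists a per-protocol limitation and promises sensitivity analyses. A separate analysis plan, not shown, may say more. Disclosure does not settle the matter: the limitation conceded concerns applicability, not bias, and it sits beside claims of overall effectiveness and attribution.

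That the completion rule acts on one arm only is an inference, but it follows directly from the absence of any control activity.

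Lastly, an all-randomised analysis is not free of assumptions. If missingness depends on the unobserved T2 score itself, a mixed model does not remove the bias. Collecting scores from adolescents who stop playing therefore matters as much as the model.

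**Conclusion.** The point holds. Per-protocol, three-wave completers are the only main analysis set named, and the treatment-completion rule can remove only game-arm adolescents after randomisation. The claims that this reduces bias and that change can be attributed to the intervention are not supported.

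The likely direction is towards emoTICare, on the assumption that adolescents who finish the game are those who would do better anyway. Under the assumptions shown, the type I error runs from 5% (no selection, or identical selection and loss in both arms) to about 25% (r = 0.3 in the game arm only, 70% versus 90% completion), with a spurious difference of 0 to 0.12 SD. A negative r reverses the sign. These figures are illustrations, not predictions for this trial.

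**What to change.** - Make the primary analysis all randomised adolescents in their allocated arm. Use a linear mixed model with T1 score, arm, time and arm-by-time and every available T2 and T3 score, or ANCOVA at T2.
- Send the T2 and T3 surveys to adolescents who stop playing.
- Delete the three-wave completion rule and LOCF. State the missing-at-random assumption and add a sensitivity analysis for departures from it.
- Keep per-protocol as a supportive analysis, and reword the bias rationale and the attribution sentence to match.
- Report withdrawals by arm with reasons, instead of using the chi-square test as reassurance.

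The cost is protocol wording, one model, survey reminders to adolescents who stopped playing, and a somewhat diluted effect estimate. The Eligibility and recruitment criteria section says no stage is complete and puts the end of data collection at February 2027, so follow-up of non-completers can still be arranged. Scores never collected cannot be recovered later.
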